## Abstract

**Background:**

Children undergoing cancer treatment are at high risk for malnutrition, poor diet quality, and early cardiometabolic risk due to treatment-related side effects, disrupted appetite, and household-level barriers to healthy eating. Caregivers play a central role in nutritional support during treatment but often experience substantial burden, time constraints, and nutrition insecurity. Food-as-medicine strategies, including medically tailored meals (MTMs), have shown promise in adult populations but remain underexplored in pediatric oncology, particularly during active treatment and within family-centered models.

**Objective:**

The primary objective of this study is to evaluate the feasibility, acceptability, and adherence of *From Kitchen to Clinic*, a 12-week, family-centered food-as-medicine intervention that integrates MTM delivery with caregiver coaching for caregivers of children undergoing cancer treatment. Secondary objectives include collecting exploratory data on patient dietary intake, weight and lean body mass trajectories, treatment tolerance, household food and nutrition security, and caregiver burden and distress to inform a future definitive trial.

**Methods:**

This prospective, single-arm feasibility study will enroll 60 caregiver–child dyads (N = 120) recruited from three outpatient pediatric oncology clinics at a large children's hospital. The 12-week intervention includes an intensive phase (weeks 1–8) with weekly MTM delivery and caregiver coaching, followed by a tapered phase (weeks 9–12) with reduced meal frequency and bi-weekly coaching. Feasibility outcomes include recruitment, retention, assessment completion, intervention adherence, and acceptability, evaluated against predefined progression criteria. Exploratory outcomes will be assessed at baseline and at 3, 6, and 12 months post-intervention using validated dietary, anthropometric, clinical, and caregiver-reported measures.

**Trial registration:**

NCT07454902.

## Introduction

1

Children undergoing cancer treatment are at high risk for malnutrition, including both undernutrition (e.g., inadequate nutrient intake, weight loss, growth faltering) and overnutrition (e.g., excess weight gain, obesity) [[1], [2], [3]]. These outcomes are driven by the side effects of chemotherapy, corticosteroids, and radiation, which disrupt appetite, metabolism, gastrointestinal function, and physical activity [1,4]. As survival rates for childhood cancers continue to improve, weight-related late effects, including obesity, insulin resistance, dyslipidemia, and other cardiometabolic abnormalities, have emerged as prevalent and clinically significant contributors to long-term morbidity, diminished quality of life, and premature cardiovascular disease among survivors [[5], [6], [7], [8], [9]].

Overweight and obesity frequently develop early during treatment, particularly among children with acute lymphoblastic leukemia, and often persist into survivorship [4,10,11]. Cardiovascular disease is now a leading non-cancer cause of morbidity and mortality among childhood cancer survivors, with risk amplified by both treatment-related cardiotoxicity and modifiable lifestyle factors such as diet quality, excess adiposity, and physical inactivity [9,12,13]. Importantly, evidence suggests that cardiometabolic risk trajectories may be established during active treatment, underscoring early therapy as a critical window for preventive intervention rather than deferring lifestyle support to survivorship alone [4,10].

Caregivers, who are often the primary source of nutritional support during treatment, face substantial stress and competing demands related to intensive treatment schedules, symptom management, and financial strain, which can limit their capacity to provide nutritionally adequate meals [3,14]. These challenges contribute to household-level nutrition insecurity and can further compromise dietary quality and treatment adherence [4,8]. Treatment-related symptoms, including dysgeusia, nausea, fatigue, mucositis, and appetite changes, frequently lead children to prefer energy-dense, highly processed foods, contributing to poor diet quality during treatment and the persistence of unhealthy dietary patterns into survivorship [1,3,4]. Compared with pre-diagnosis dietary behaviors, children undergoing cancer treatment often consume inadequate fruits and vegetables and excess ultra-processed foods, patterns that may compound long-term cardiometabolic risk [1,8,15].

Diet quality is a modifiable risk factor for cardiometabolic health among childhood cancer survivors. Observational evidence suggests that greater adherence to healthy dietary patterns is associated with more favorable cardiovascular risk profiles in survivors, particularly those already exposed to cardiotoxic therapies [8]. Early lifestyle interventions initiated during cancer treatment have been shown to be feasible and safe, with emerging evidence of modest improvements in dietary intake and cardiometabolic markers; however, sustained, scalable, and family-centered nutrition interventions during active treatment remain limited [4,10].

Food-as-medicine interventions, particularly medically tailored meals (MTMs), are gaining momentum as promising strategies to address both medical and social needs through food-based healthcare [3,16]. MTMs provide convenient, nutritionally appropriate meals aligned with treatment goals while directly addressing barriers common during pediatric cancer treatment, including food access constraints, caregiver time scarcity, treatment-related fatigue, and symptom-driven food preferences. [14,16] In adult populations with nutrition-sensitive chronic conditions, MTMs have been shown to improve diet quality, reduce food insecurity, and, in some studies, lower disease-specific hospitalizations and short-term mortality, although effects on overall healthcare utilization have been mixed [[17], [18], [19]]. Although evidence from oncology populations remains limited, emerging qualitative and mixed-methods evidence suggests that MTMs, particularly when paired with nutrition counseling, may support patient engagement, reduce food-related stress, and facilitate active coping and behavior change during active cancer treatment; however, such studies remain few and have largely been limited to adult populations [16,20]. Despite strong theoretical alignment with the needs of pediatric oncology populations, MTMs and other food-as-medicine approaches remain underexplored in children undergoing cancer treatment, particularly as part of early, family-centered preventive strategies.

### Objectives

1.1

Taken together, these findings highlight a critical gap in pediatric oncology care: the lack of pragmatic, family-centered nutrition interventions initiated during active treatment that address both treatment-related symptoms and household-level barriers to healthy eating. To address this gap, we developed *From Kitchen to Clinic*, a family-centered, food-as-medicine intervention that integrates MTMs with caregiver coaching. The primary objective of this feasibility study is to provide evidence for the feasibility, acceptability, and adherence of a 12-week food-as-medicine intervention, combining MTM delivery with caregiver coaching. The secondary objective is to collect exploratory outcome data on patient dietary intake, patient weight outcomes, and treatment tolerance; household food and nutrition security; and caregiver burden and distress. These data will be used to estimate variability, assess measurement procedures, and identify potential signals of intervention effect to inform the selection of outcome measures and sample size calculations for a future trial.

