### Study design

2.1

This is a prospective single-arm feasibility study and will include children on active cancer treatment and caregivers (n = 60 dyads). Caregiver-child dyads, where caregiver is defined as a parent or legal guardian of the child receiving treatment for cancer, will be recruited from three outpatient oncology clinics at the Children's Hospital of Philadelphia (CHOP). This study was approved by the Institutional Review Board at CHOP (IRB 26-024340) and registered at ClinicalTrials.gov (NCT07454902). See Fig. 1 for the study schema.

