### Data analysis plan

2.8

Feasibility and acceptability will be evaluated as the primary outcomes and interpreted relative to predefined progression criteria (Table 2), consistent with published guidance for pilot and feasibility studies [22,23]. Criteria encompass recruitment, retention, assessment completion, intervention adherence, and acceptability and were selected based on prior literature, anticipated caregiver burden, and intervention logistics. Feasibility will be considered established if at least four of the five criteria are met, supporting progression to a future definitive trial.

Descriptive statistics will be selected based on variable type and distribution. Continuous variables will be summarized using means and standard deviations or medians with interquartile ranges, as appropriate, while categorical variables will be described using frequencies and percentages. Acceptability items measured on 5-point Likert scales (1 = strongly disagree to 5 = strongly agree) will be summarized using medians and interquartile ranges, with a median score ≥4.0 indicating acceptable or useful intervention components. Frequencies and percentages will also be presented to enhance interpretability. Distributional assumptions will be assessed through visual inspection.

Secondary endpoints will examine exploratory clinical and behavioral outcomes, including changes in patient dietary intake, weight and lean body mass trajectories, and treatment tolerability. Additional secondary outcomes will include changes in household food and nutrition security and caregiver burden and distress. Given the pilot nature of the study, these outcomes will be analyzed descriptively by comparing pre- and post-intervention measures to inform future hypothesis-driven trials.

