## Discussion

3

This protocol describes *From Kitchen to Clinic*, a prospective, single-arm feasibility study evaluating a 12-week, family-centered food-as-medicine intervention for caregivers of children undergoing cancer treatment. The intervention integrates MTM delivery with caregiver coaching, delivered during a critical period following diagnosis when treatment intensity, caregiver burden, and nutrition-related challenges are often greatest. The stepped intervention design - featuring an intensive phase followed by a tapered transition phase - was intentionally selected to balance early support with skill-building and sustainability, while minimizing participant burden.

Despite growing recognition of nutrition as a modifiable contributor to long-term survivorship outcomes, there remains a lack of pragmatic, family-centered nutrition interventions delivered during active pediatric oncology treatment. *From Kitchen to Clinic* addresses this gap by combining MTMs with caregiver coaching to reduce structural and psychosocial barriers to healthy eating. By intervening early, during active treatment rather than survivorship alone, this study aligns with emerging evidence suggesting that dietary patterns, weight trajectories, and cardiometabolic risk may be established during treatment and persist thereafter. This protocol contributes to the limited but growing literature on food-as-medicine approaches in oncology and represents one of the few studies to examine MTMs within a pediatric, family-centered model.

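### Uncontrolled before-after change is named as a source of effect signals for the future trial's outcomes and sample size, but one arm cannot separate effect from the treatment course

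*Protocol article*

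**What the plan says.** Section 1.1 (Objectives) gives the exploratory data three uses. Two are stated as "These data will be used to estimate variability, assess measurement procedures". The third is to "identify potential signals of intervention effect to inform the selection of outcome measures and sample size calculations for a future trial".

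Section 2.1 describes a prospective study with one arm and 60 dyads. Section 2.8 (Data analysis plan) says the secondary outcomes will be "analyzed descriptively by comparing pre- and post-intervention measures to inform future hypothesis-driven trials". No concurrent, historical or external comparison is described.

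The article also describes how these outcomes relate to treatment:

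- **Nutrition and weight (section 1):** of under- and overnutrition it says "These outcomes are driven by the side effects of chemotherapy, corticosteroids, and radiation, which disrupt appetite, metabolism", and on timing, "Overweight and obesity frequently develop early during treatment, particularly among children with acute lymphoblastic leukemia, and often persist into survivorship".
- **Caregivers (section 3, Discussion):** the programme is "delivered during a critical period following diagnosis when treatment intensity, caregiver burden, and nutrition-related challenges are often greatest".
- **Entry (section 2.3):** the child must be expected to have at least 12 more weeks of treatment. No upper limit on time since diagnosis is set, and section 2.4 collects relapse status, so entry points may differ.
- **Follow-up (section 2.6):** assessments run to 12 months.

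**The concern.** A before-after change in one group is the sum of whatever the programme did and whatever would have happened anyway. Where outcomes are stable without intervention, the second part may be small. The protocol gives its own reasons to think these outcomes are not stable: it ties weight and nutrition to chemotherapy, corticosteroids and radiation, and places caregiver burden at its highest in the window the programme targets.

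Two decisions about the definitive trial are at stake. If observed change guides outcome selection, a measure that moves with treatment may look responsive, and one where the programme offsets a worsening may look inert. If observed change is used as the planning difference, the definitive trial may be sized on a quantity that is partly or wholly natural course.

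**Working it through.** **The plan's own figure.** Section 2.2 justifies 60 dyads by convention for feasibility studies and gives no alpha, power, effect size or target precision. The only arithmetic to reproduce is 60 × 2 = 120 participants, which is correct. No stated figure is overturned.

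**Identification.** For each outcome,

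expected before-after change = programme effect + natural change.

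One arm gives one equation in two unknowns. A larger sample estimates the left side more precisely but does not split the right side.

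**Inputs for an illustration.**

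- SD = 10 on the PROMIS T-score, the general-population value in section 2.7.2.
- Two-sided alpha 5% and power 80%: assumed for the future trial.
- True effect of 2 points, natural change of 0 to 3 points in the same direction: assumed. The document gives neither, so a range is shown.

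**Formulas.** Per-arm size for a planning difference D:

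n = 2 × (1.960 + 0.842)² × 10² / D² ≈ 1570 / D², rounded up.

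Real power when the true difference is 2:

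power = Φ(2/10 × √(n/2) − 1.960).

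**Results.**

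| Natural change | Observed change used as D | Planned per arm | Needed per arm | Real power |
|---|---|---|---|---|
| 0 | 2 | 393 | 393 | 80% |
| 1 | 3 | 175 | 393 | 46% |
| 2 | 4 | 99 | 393 | 29% |
| 3 | 5 | 63 | 393 | 20% |

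For the third row: 1570/16 = 98.1, so 99 per arm; 0.2 × √49.5 = 1.407; Φ(1.407 − 1.960) = Φ(−0.553) = 0.29.

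With a true effect of 3 points (175 per arm needed), the same 1, 2 and 3 points of natural change give 99, 63 and 44 per arm and real power of 56%, 39% and 29%.

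**Apparent signals with no effect.** Assume a within-person correlation of 0.5. The SD of change is 10 × √(2 × 0.5) = 10, and the standard error at n = 60 is 10/√60 = 1.29. A natural change of 2 points with no programme effect would give a 95% interval excluding zero about 34% of the time, and one of 3 points about 64%. At 45 dyads (75% of 60, the retention threshold) the figures are 27% and 52%.

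**Adverse drift.** If natural change runs against the programme, a true 2-point benefit with 2 points of worsening gives an expected observed change of 2 − 2 = 0, and the benefit is not seen.

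**The case against.** The best defence is that the protocol is already cautious. Section 2.2 says the study is not powered for effects. The outcomes are exploratory and analysed descriptively, and the objective speaks only of potential signals. Effectiveness is left to a later randomised trial, and no exploratory change enters the progression rule in Table 2. All of this stands and limits the weight of the point. But lack of power concerns precision, while the problem here is attribution. The Discussion's single-arm caveat concerns the untested feasibility and acceptability of a comparison condition, and how assignment to a non-meal arm might affect a future trial. Nowhere does the article say that change in this study cannot be credited to the programme.

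A second defence is that the three uses in section 1.1 are listed together, so the link to sample size could be met by variability alone. That is fair. A reader might infer that the authors have committed to using the observed change as the planning effect size, and the text does not say so. It does, however, name effect signals as one of the inputs and does not exclude that use.

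A reader might also infer specific directions: that anxiety, nutrition security and diet would recover unaided, that BMI z-score would rise, or that every family starts at a peak of burden. The document does not support these. Section 1 describes both weight loss and excess gain, and unhealthy eating that persists into survivorship. The remark in section 2.5 about routines stabilising explains the meal taper and says nothing about anxiety. Open entry with respect to time since diagnosis argues against a common peak. None of this restores attribution; it means the sign of the bias is unknown.

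**Conclusion.** The point holds as a stated use that the design cannot support. It is of moderate weight: it should be corrected, but it does not touch the primary feasibility objective or the progression decision. Estimating variability and testing measurement procedures are sound uses of a single arm and are not in question.

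The conclusion itself needs only the single-arm design and the protocol's own account of treatment-driven change. The size does not come from the document. The fall to 175–63 per arm against about 393, and to 46%–20% power, assumes a true 2-point effect, SD 10, 1 to 3 points of natural change in the same direction, and a planner who takes the observed change at face value. It shows how sensitive planning is to modest drift of 0.1 to 0.3 SD; it is not a forecast for this study.

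**What to change.** **Section 1.1.** Remove the clause on signals of effect, or replace it with: *describe change over time, which cannot be attributed to the intervention*.

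**Section 2.8.** Add that:

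- from these outcomes, only the SD, within-person correlation, completeness and floor or ceiling behaviour of each measure will inform the future sample size;
- the target difference will come from a clinically important difference or from controlled data, not from the observed before-after change;
- observed change alone will not decide the future primary outcome, though it may be considered alongside other evidence.

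Describing change by treatment phase, using chart data already collected, would help interpretation but is optional.

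**Cost.** Wording in two sections, with no new participants, visits or measures. The study gives up a preliminary-effect claim.

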## Methods

2

### Study design

2.1

This is a prospective single-arm feasibility study and will include children on active cancer treatment and caregivers (n = 60 dyads). Caregiver-child dyads, where caregiver is defined as a parent or legal guardian of the child receiving treatment for cancer, will be recruited from three outpatient oncology clinics at the Children's Hospital of Philadelphia (CHOP). This study was approved by the Institutional Review Board at CHOP (IRB 26-024340) and registered at ClinicalTrials.gov (NCT07454902). See Fig. 1 for the study schema.

**Fig. 1 fig1:**
[figure not shown]
Study schema.

### Study population and sample size

2.2

In this study, caregiver-child dyads in which the child is actively receiving cancer treatment will be invited to participate in a food-as-medicine intervention. Consistent with the aims of early-phase research, this feasibility study is not powered to detect statistically significant intervention effects; rather, its primary purpose is to assess feasibility and acceptability and to generate data that will inform the design of a subsequent, fully powered trial. A total of 60 caregiver-child dyads (N = 120; 60 children and 60 caregivers) will be enrolled using convenience sampling.

This sample size is consistent with methodological recommendations for pilot and feasibility studies, which suggest that samples of approximately 50-60 participants are common and adequate for evaluating key feasibility outcomes such as recruitment, retention, intervention adherence, and acceptability, particularly when multiple feasibility indicators are of interest [21,22]. Prior reviews of feasibility studies report a median total sample size of approximately 60 participants and note that samples in this range are sufficient to characterize feasibility parameters with reasonable precision while minimizing participant burden and resource use [22]. The proposed sample will allow estimation of feasibility metrics and associated confidence intervals to guide progression criteria and inform planning of a future randomized trial.

### Eligibility criteria

2.3

Patients must be anticipated to receive treatment for their cancer diagnosis for at least 12 weeks. Children must be between five and 21 years of age at the time of enrollment, be able to speak English, and be approved to participate from the study's clinical Principal Investigator (PI). Patients must be anticipated to reside in the same household as their designated caregiver for the duration of the study. Patients will be excluded if they have swallowing or digestive disorders, food allergies (e.g., celiac disease, lactose intolerance, nut allergy), or specific food preferences that cannot be accommodated by the meal provider; have a diagnosis managed by neuro-oncology or a diagnosis of Acute Myeloid Leukemia (AML); or are undergoing bone marrow transplantation.

Eligible caregivers must be a parent or legal guardian of a child who meets all patient inclusion and exclusion criteria. Caregivers must be at least 18 years of age, able to read and speak English, have access to an internet-enabled device (e.g., smartphone, tablet, laptop, or desktop computer), and have the capacity to provide informed consent. Caregivers must also be anticipated to reside in the same household as the participating child for the duration of the study, and must live within the Metropolitan Area Neighborhood Nutrition Alliance (MANNA) meal delivery radius. Individuals who do not meet all eligibility criteria will not be enrolled.

### Consent and enrollment

2.4

Potentially eligible caregiver–child dyads will be identified in collaboration with the pediatric oncology care team and screened for eligibility by study staff. Families meeting preliminary eligibility criteria will be approached during routine clinical encounters or contacted by phone or secure electronic communication. Study staff will provide a detailed explanation of the study purpose, procedures, risks, and benefits and allow sufficient time for questions prior to enrollment.

Written informed consent will be obtained from caregivers for both caregiver and child participation. For pediatric participants younger than 18 years of age, parental permission will be obtained from the caregiver, and written informed assent will be obtained from children aged 7 years and older, in accordance with institutional policies. Written HIPAA authorization will be required for child participation, as study staff will extract selected demographic and clinical information from the electronic medical record, including age, sex, race and ethnicity, diagnosis, treatment details, date of diagnosis, relapse status, cancer type and treatment at first diagnosis if relapse has occurred, and zip code of residence.

Enrollment will occur only after confirmation of eligibility and receipt of all required consent, assent, and authorization documents. Participation is voluntary, and caregivers and patients may withdraw at any time without impact on clinical care. All consent and enrollment procedures will be conducted in accordance with institutional review board approval.

